#### Secondary outcome measure

Secondary outcomes are the following:
Time to clinical improvement of symptoms (TTCIS) [time frame: baseline to day 14].Participants assessed the severity of 7 influenza-associated symptoms (cough, sore throat, headache, nasal congestion, feverishness/chills, muscle/joint pain, and fatigue) on a 4-point scale (0 = no symptoms, 1 = mild, 2 = moderate, and 3 = severe). TTCIS was defined as the time from the start of treatment to the time when all influenza symptoms were alleviated, as defined below, for a duration of at least 21.5 h:• Pre-existing symptoms (cough, fatigue, or muscle/joint pain that existed prior to influenza) that were worse at baseline must have improved at least 1 point from baseline.• New symptoms must have alleviated, defined as a symptom score of none (0) or mild (1).Time to defervescence (TTD) [time frame: baseline to day 14].Time to defervescence includes defervescence onset time and the time to complete defervescence. Defervescence onset time is defined as the time from the start of treatment to the time when the body temperature decreases to ≤37.3 °C. And complete defervescence is defined as the time from the start of treatment to the time when the temperature of ≤37.3 °C sustained for ≥ 24 h [14, 28].Percentage of participants with 2 or more Influenza-related complications [time frame: baseline to day 28].Secondary influenza complications include pneumonia, encephalitis, meningitis, encephalopathy, myelitis, Guillain-Barré syndrome, myocarditis, pericarditis, myositis, and septic shock.Percentage of participants whose symptoms were improved at each time point [time frame: 12, 24, 36, 48, 72, 96, 120, 144, and 168 h after the initial dose of study treatment]. The criteria for improvement of influenza symptoms have been described above.Percentage of participants reporting normal temperature at each time point [time frame: 12, 24, 36, 48, 72, 96, 120, 144, and 168 h after the initial dose of study treatment]. Defined as the percentage of participants whose axillary body temperature dropped to equal or less than 37.3 °C after the initiation of the study treatment.Body temperature at each time point [time frame: 12, 24, 36, 48, 72, 96, 120, 144, and 168 h after the initial dose of study treatment]. Participant’s self-measured axillary temperature using an electronic thermometer.Percentage of participants requiring systemic antibiotics for infections secondary to influenza [time frame: day 2 to day 28].Percentage of participants with adverse events (AEs).Inpatient length of stay defined as number of days in hospital [time frame: day 2 to day 28].Median time (days) receipt of oxygen [time frame: day 2 to day 28].

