### Sample size {14}

Sample size calculations are based on the primary endpoint (the proportion of clinical improvement within 7 days after randomization). At the 5% significance level, a total of 101 patients per group is required to achieve 90% power and to determine an increase of 20% in the proportion of clinical improvement between *QZQG* group and the placebo group, assuming that the clinical improvement rate within 7 days after randomization of the placebo group receiving oseltamivir plus routine symptomatic treatment is about 50%. With an estimated dropout rate of 10–20%, a total of 228 patients are planned to be enrolled. If the initial hypothesis is not rejected, subsequent comparison is considered exploratory, and no conclusion is made.

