## Statistical methods

### Statistical methods for analyzing primary and secondary outcomes {20a}

The primary study analysis will occur when the last patient has either withdrawn or completed day 28 visit, and will be based on cleaned data for all patients up to and including this point. The clinical data will be managed and analyzed by the independent statisticians from a third party (School of Public Health, Fudan University,) in accordance with the statistical analysis plan. Data management and analysis will use SAS V.9.4 (SAS Institute, Cary, NC, USA).

All statistical inferences will be determined using two-sided tests. *P* < 0.05 will be considered significant, and 95% confidence intervals will be used. Data will be described as the mean, standard deviation, and confidence intervals. If necessary, minimum, maximum, P25, P75, and median values will be provided. Paired measurement data will also show the differences between the mean and standard deviation. When using nonparametric methods, median and mean values will be provided. Count data will be described using the frequency distribution and corresponding proportion. Qualitative information will be described using the positive rate, the number of positive cases, and the denominator.

Baseline data analyses (in FAS and PPS) will include demographic indicators and primary and secondary outcomes before intervention. Measurement data will be described using a *t*-test or *t*’ test (if the variance is absent). Count data will be described using the Pearson’s *χ*^2^ test. Rating data will be described using the two-sample Wilcoxon rank sum test.

Logistic regression model will be used to explore the efficacy (*QZQG* group and placebo group) and factors affecting efficacy. Dependent variable is the proportion of clinical improvement at day 7. In addition to drugs, independent variables also include the basic information and life behavior factors of participants. The basic information includes gender, height, weight, age, and underlying diseases that include chronic obstructive pulmonary disease, asthma, diabetes, hypertension, hyperlipidemia, hyperuricemia, cardiovascular disease, autonomic nervous dysfunction, lung cancer, other tumors, etc. Life behavior factors mainly include smoking and drinking.

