### Methods for any additional analyses {20b}

Subgroup analysis of all endpoints will be conducted based on chronic respiratory diseases (with or without), complications (with or without) and course of disease (< 3 days and ≥ 3 days). Subgroup analyses will be produced where appropriate and where the number of patients in each subgroup is sufficient.

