The choice of the primary outcome for RCTs is important and challenging for the rational evaluation of the test drug. Adults with severe influenza have various clinical outcomes, including discharge, hospitalization without oxygen, hospitalization requiring respiratory support or ECMO, and even death. We believe that a single end point (the duration of viral shedding, the time to clinical symptom alleviation, etc.) may not accurately assess the effect of the test drug. Therefore, 7-category ordinal scale and NEWS2 as composite clinical outcome used in severe influenza trial before [26, 36] is required for the evaluation of the efficacy of *QZQG*, which is both pragmatic and informative [37]. At the same time, a range of secondary endpoints to show consistency with the primary endpoint have been included in this trial, as recommended by the US Food and Drug Administration for trials in influenza [38].

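### The gatekeeping rule covers only a failed primary; after a positive primary, at least 26 secondary efficacy comparisons and the subgroup analyses are open to claims at two-sided 0.05 with no order or error control

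*Protocol article*

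**What the plan says.** Sample size {14} describes the primary comparison and then closes with the only rule on later ones: "If the initial hypothesis is not rejected, subsequent comparison is considered exploratory, and no conclusion is made". The article has no matching sentence for a rejected primary hypothesis.

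Statistical methods for analyzing primary and secondary outcomes {20a} sets one standard for everything: "All statistical inferences will be determined using two-sided tests", with significance declared below 0.05.

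The Secondary outcome measure section lists ten outcomes without ranking them. Several are read repeatedly, for example "Percentage of participants whose symptoms were improved at each time point [time frame: 12, 24, 36, 48, 72, 96, 120, 144, and 168 h".

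Methods for any additional analyses {20b} adds: "Subgroup analysis of all endpoints will be conducted based on chronic respiratory diseases (with or without), complications (with or without) and course of disease". The stated limits are that these be appropriate and that the subgroups be large enough.

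The Discussion gives the secondaries a supportive purpose: "a range of secondary endpoints to show consistency with the primary endpoint have been included in this trial". It does not call them exploratory.

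**The concern.** A rule that withholds conclusions only after a failed primary gives weak control. If QZQG has no effect on anything, a claim requires a false-positive primary first, so the overall error stays at or below 5%. If QZQG does improve the primary outcome, which is the situation the trial is powered for, the gate opens and nothing limits false claims among those secondaries that are in fact null.

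At stake is the reading of the secondary results. A difference at one of nine symptom or temperature times, or in one subgroup, could be reported as an established finding under the protocol's own criterion when it is chance.

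**Working it through.** **The plan's own figures.** The article gives no familywise error rate to reproduce. The figure in the same section, 101 per group for 50% versus 70% at 90% power, does not enter this check. (It reproduces with a one-sided 5% test; a two-sided test gives 124. That is a separate matter.)

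**Step 1: count the secondary efficacy comparisons** from the Secondary outcome measure section, leaving out adverse events.

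| Outcome | Comparisons |
|---|---|
| Time to clinical improvement of symptoms | 1 |
| Time to defervescence (onset, complete) | 2 |
| Two or more complications | 1 |
| Symptoms improved, 9 time points | 9 |
| Normal temperature, 9 time points | 9 |
| Body temperature | 1 (or 9) |
| Systemic antibiotics | 1 |
| Length of stay | 1 |
| Time on oxygen | 1 |
| **Total** | **26 (or 34)** |

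Body temperature counts once because {20a} plans repeated-measures analysis for quantitative variables. Testing it at each time gives 26 − 1 + 9 = 34.

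**Step 2: count the subgroup comparisons.** Three factors with two levels give 6 subgroups. Applied to the 26 secondaries, that is up to 26 × 6 = 156 further comparisons. This is a ceiling, because {20b} drops subgroups that are too small.

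**Step 3: chance of at least one false positive among k null secondaries**, each at two-sided 0.05.

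- Independent tests: 1 − 0.95^k. For k = 26, 1 − 0.95^26 = 73.6%; for k = 34, 82.5%.
- Equal correlation ρ between test statistics: 1 − ∫ [Φ((1.96 − √ρ·t)/√(1−ρ)) − Φ((−1.96 − √ρ·t)/√(1−ρ))]^k φ(t) dt.

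The correlations are assumptions, since the document gives none.

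| Null tests | ρ = 0 | ρ = 0.5 | ρ = 0.8 | ρ = 0.9 |
|---|---|---|---|---|
| 26 | 74% | 48% | 24% | 17% |
| 34 | 83% | 53% | 27% | 18% |
| 10 | 40% | 29% | 17% | 13% |
| 26, errors favouring QZQG only | 48% | 24% | 12% | 8% |

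The row for 10 shows how the rate falls if only ten of the comparisons are null.

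**Step 4: a second correlation structure.** Letting correlation decay along each nine-point series (0.7 to 0.95 between adjacent times) with 0 to 0.7 between endpoints gives 24% to 65% for the 26 secondaries. Among trials whose primary is significant at 90% power, it gives 20% to 65%.

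**Step 5: everything null, including the primary.** In simulation, the chance of a significant primary together with a significant secondary stays below 5%. The inflation therefore belongs to the case where the primary effect is real.

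**The case against.** Ranking and adjusting secondary outcomes is commonly left to the statistical analysis plan, which is not shown, and this is a condensed article. What it does fix is sensible: one primary outcome, and no conclusions if that fails. The text never says that each secondary becomes conclusive after a positive primary; that is inferred from its silence. The Discussion gives the secondaries a supportive role, which one isolated time point out of nine would hardly fill. The subgroups sit under additional analyses and promise no claim.

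Part of this stands. The absence of a named multiplicity method is not the finding. The finding is that the article itself fixes a one-sided gate and a 5% criterion for all inferences, and together these leave the success branch open.

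Three stronger readings are tempting and are not supported:

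- **That a false secondary claim is likely.** The 18 time-point proportions restate the symptom and temperature outcomes in the same patients, so correlation should be substantial, and at 0.5 or above the rate is below one half. All the rates also take every secondary as null while the primary works. That is a worst case: the ordinal scale rests on hospitalization and oxygen need, which overlap with length of stay and time on oxygen.
- **That the subgroup plan by itself produces false positives at a high rate.** With no treatment effect, the gate keeps subgroup claims to about 5% of trials. With a uniform true effect, a significant subgroup is a true positive, and a mix of significant and non-significant levels reflects low power.
- **That a failed primary leaves safety unanswered.** Safety has its own analysis set in {20c}, its own comparison and listings in {20a}, and its own assessment under Harms {22}. None is made to depend on the primary.

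**Conclusion.** The point holds as a gap in the decision rule. The stated rules leave at least 26 secondary efficacy comparisons, and the subgroup analyses of all endpoints, open to claims of significance once the primary is positive. The 17% to 48% range rests on three assumptions: all 26 secondaries null, equal correlation between 0.5 and 0.9, and two-sided counting in either direction. Relaxing the first lowers it, and counting only errors in QZQG's favour about halves it to 8% to 24%. Even the lowest of these figures exceeds the nominal level for one test in the same direction (2.5%). No error rate is attached to the subgroups here. The primary analysis and its 5% level are untouched, so this is an inexpensive improvement to how secondary results may be read and does not threaten the main conclusion.

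**What to change.** Extend the closing sentence of Sample size {14} to cover the success branch, and carry the same text into {20a} and {20b}:

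- If the primary hypothesis is rejected, a short list of key secondary outcomes is tested in a pre-specified order, each at two-sided 0.05, stopping at the first non-significant result. The sponsor chooses the list and order before unblinding; the document ranks none, so the choice is the sponsor's.
- All other secondary outcomes, all individual time-point comparisons and all subgroup analyses are exploratory, reported as estimates with 95% confidence intervals and without claims of significance.
- Differences between subgroups are judged by the treatment-by-subgroup interaction, not by P values within each level.

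The fixed sequence keeps the chance of any false claim among the key secondaries at or below 5%, because the first null outcome in the order is tested at 0.05 and a non-significant result ends testing. By comparison, a Bonferroni split over all 26 would put each test at 0.05/26 = 0.0019.

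The cost is wording only: no new data, visits or patients. The loss is that outcomes off the list, or below the first failure in the order, can no longer be claimed as significant.

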### Recruitment {15}

Patients will be recruited from 10 clinical centers most of which are the designated hospitals for patients with severe influenza.

## Assignment of interventions: allocation

### Sequence generation{16a}, concealment {16b}, and implementation {16c}

According to a stratified block randomization method, all patients are stratified by study center and randomly assigned to the *QZQG* group and placebo group in a 1:1 ratio. The random sequence and the randomization list of every center will be generated by the independent specialist from School of Public Health, Fudan University, China using the PRCO PLAN function of the analysis system of SAS software (SAS, Cary, NC, USA). The randomization sequence will be concealed in a lightproof sealed envelope for emergency unblinding events, which will be kept by the independent specialist and the Sponsor. An independent drug administrator at every center will assign numbered packs of study drugs to eligible patients in order by randomization list.

An emergency letter including the random sequence and assignment has been prepared in all of centers. In any emergency medical situation, such as serious adverse event or deteriorative condition, the unblinding process will be started after contacting the Sponsor and the primary investigator. The investigators from Longhua Hospital Affiliated to Shanghai University of traditional Chinese Medicine will record the details of urgent unblinding and make sure the corresponding patient is excluded. If the rate of drug blinding leakage or emergency letter opening rises more than 20%, this trial will be considered as failure.

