### Circumstances and procedure for unblinding if needed {17b}

Unblinding is permissible in emergency situations when investigators believe that it is necessary to perform any agent treatment/action for the trial patient’s safety. To allow emergency unblinding the investigator will be supplied with a set of emergency envelopes. If emergency unblinding of a patient is necessary, an independent pharmacist opens the sealed envelope and informs the investigators of the allocation. And the pharmacist has to enter date and time as well as his/her name and signature on the unblinding form contained in the envelope. Information about the date, time, and reason of unblinding will be recorded in Clinical Case Forms (CRFs) and the envelope.

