#### Assessment of adverse events

Any adverse event that occurs to a participant will be recorded in the CRF regardless of relationship to the intervention. Adverse events are divided into three levels: mild, moderate and severe (Table 3). And the adverse events are not necessarily related to the drugs. Any cause-and-effect relationship between adverse events and the study drugs will be determined by the classifications as shown in Table 4. If patients with mild or moderate adverse events do not show significant improvement after medical treatment or drug reduction, the research doctors need to report to the ethics committee and terminate the trial. All serious adverse events will be reported within 24 h to the Principal Investigator, Steering Committee, IRB, the sponsor, and CFDA.

**Table 3 Tab3:** Classification of disease severity

Classification	Features
**1. Mild**	Participants can continue to participate in the trial without medical treatment and impact on the health.
**2. Moderate**	Participants could not tolerate the drug or need medical treatment. Such events partially affect the participants’ functional activity without threat to life safety.
**3. Severe**	The events pose threat the life of participants, leading to death or disability, which requires immediate withdrawal of medicine or emergency monitoring treatment.

**Table 4 Tab4:** Classification of the correlation between adverse events and drugs

Classification	Features
**1. Definite**	Use of the experimental drug has a definite relationship with time.
	The event is consistent with the known adverse reactions of Chinese herbal medicine.
	Adverse events disappear after drug withdrawal and reappear after repeated administration.
**2. Probable**	Use of the experimental drug has a reasonable relationship with time.
	Adverse events are partially in line with the known adverse reactions of Chinese herbal medicine.
	It is difficult to identify a cause owing to disease or other reasons.
**3. Possible**	Use of the experimental drug has a reasonable relationship with time.
	Adverse events do not conform to adverse reactions of Chinese herbal medicine.
	The adverse events are likely to be caused by diseases or other reasons.
**4. Remote**	There is a possible connection between time and experimental drug.
	It is easily explained and verified through the disease or other reasons.
**5. Unrelated**	There is no connection between time and the test drug.

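### Emergency unblinding must wait for contact with the Sponsor and the primary investigator, with no exception for urgency, and the dedicated unblinding section leaves this step out

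*Protocol article*

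**What the plan says.** Two sections of the protocol article govern emergency unblinding.

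- **Sequence generation {16a}, concealment {16b}, and implementation {16c}.** The site holds the means to unblind: "An emergency letter including the random sequence and assignment has been prepared in all of centers". The rule for using it has a wide scope, "In any emergency medical situation, such as serious adverse event or deteriorative condition", and a fixed order: "the unblinding process will be started after contacting the Sponsor and the primary investigator". The section also has the sealed randomisation sequence kept by the independent specialist and the Sponsor, and it treats the trial as failed if blinding leakage or letter opening exceeds 20%.
- **Circumstances and procedure for unblinding if needed {17b}.** The trigger is the investigators' judgement: "Unblinding is permissible in emergency situations when investigators believe that it is necessary to perform any agent treatment/action for the trial" patient's safety. The means are again local: "To allow emergency unblinding the investigator will be supplied with a set of emergency envelopes". When the code is needed, "an independent pharmacist opens the sealed envelope and informs the investigators of the allocation". On documentation: "Information about the date, time, and reason of unblinding will be recorded in Clinical Case Forms (CRFs) and the envelope". The section does not mention the Sponsor or the primary investigator, before or after the opening.

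Two other places matter. Under Assessment of adverse events, "All serious adverse events will be reported within 24 h to the Principal Investigator, Steering Committee, IRB, the sponsor, and CFDA". The text after Table 4 says that if a participant becomes critically ill, the trial drug is stopped, treatment starts immediately, and the sponsor and ethics committee are told within 24 h.

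**The concern.** The allocation section makes contact with two parties a precondition for breaking the blind in any emergency. It does not say what to do if the matter cannot wait or if one of them does not answer. Staff who work from {17b} would have the pharmacist open the envelope at once. Staff who work from the allocation section would first contact the Sponsor and the primary investigator.

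At stake is a possible delay in obtaining the allocation when it matters for the patient. {17b} accepts that such cases exist, because it permits unblinding only where a treatment or action for safety requires it. The Safety assessment section names allergic reactions as a possible effect of the herbal medicine, and every patient also takes oseltamivir. In a suspected drug reaction the allocation could therefore inform which drug to blame and withhold.

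**Working it through.** No arithmetic beyond a count applies. The check sets the sections side by side and then looks for an override elsewhere.

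| Step | Allocation section {16a}–{16c} | Unblinding section {17b} |
|---|---|---|
| Scope or trigger | Any emergency, with serious adverse events and deterioration as examples | Emergency in which investigators judge unblinding necessary for safety |
| Where the code is | Emergency letter in every center; sealed sequence also with the specialist and the Sponsor | Emergency envelopes supplied to the investigator |
| Contacts before opening | 2 (Sponsor, primary investigator) | 0 mentioned |
| Exception for urgency or an unreachable party | None | None |
| Time limit on contact | None | None |
| Who opens | Not stated | Independent pharmacist |

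1. **Order of steps.** The allocation section makes contact come first. The difference in required contacts is 2 − 0 = 2, where the zero reflects silence and not an express waiver.
2. **Search for an override.** The criteria for discontinuing or modifying treatment {11b} deal with halting study drug. The blinding section {17a} says only who is blinded and that assignments are unblinded after database lock. The adverse-event section and the critical-illness text set 24 h reporting duties. None of these relaxes the contact step.
3. **Is the contact needed to obtain the code?** No. Both sections place an emergency code at the site, and {17b} names the person who opens it.
4. **Combined reading.** Because {17b} is silent, the sections can be followed as one sequence: the investigator judges the need, contacts both parties, and the pharmacist opens the envelope. This removes any outright contradiction but keeps the unconditional precondition.
5. **Length of the delay.** If the rule means an attempt at contact, the delay is the time of two calls. If it means contact made, the delay has no upper limit when a party cannot be reached. The text does not settle which is meant.
6. **Number of patients.** The documents give no rate of emergencies in which the allocation is needed, so no number can be calculated.

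**The case against.** The strongest case against the point has four parts.

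- **The sections do not contradict each other, and contact is not approval.** Both statements are correct. {17b} need not repeat a step given just before it, and nobody is given a veto. The precondition nevertheless remains, so this limits the point without removing it.
- **The missing detail belongs in the full protocol or site instruction.** A journal article may leave out a definition of contact or a fallback for an unanswered call. What the article does state is an order of steps that applies to any emergency. That order is on the page, and the point concerns it.
- **The Sponsor holds an envelope, so contacting the Sponsor may serve a purpose.** This is a fair reading of the allocation section. Because every center has a letter and the investigator has envelopes, the Sponsor's copy is not needed to learn the allocation.
- **The harm is speculative.** This largely stands. Study drug can be halted and care begun without the code, and patients are inpatients under a research doctor's management. The placebo is itself a 20-fold dilution of the formula, so a placebo allocation would not exclude herbal exposure in a suspected allergy. The documents describe no case in which two calls would change the outcome.

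The choice between notifying first and notifying afterwards is partly one of policy. The protocol itself prefers acting first in neighbouring situations: treatment of critical illness starts immediately, and the Protocol amendments section {25} lets changes that remove an immediate hazard proceed before IRB approval, with prompt notice.

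**Conclusion.** The concern holds as a small, cheap improvement. The allocation section fixes the order of steps badly: in any emergency it puts contact with two parties before use of a code that the site already holds, with no way round for urgency or an unreachable party. {17b} omits the step, so it gives site staff no help with it.

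The effect is a possible delay, between two calls and no upper limit depending on how the rule is read, in the few emergencies where the allocation bears on care. It does not affect the sample size, power, type I error or any estimate.

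The conclusion rests on the published article. It assumes that no site instruction already permits immediate opening and that the emergency letters and envelopes are at the centers as stated.

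**What to change.** Replace the contact sentence in the allocation section with a rule such as:

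> When the investigator judges that the allocation is needed for the patient's safety, the independent pharmacist opens that patient's envelope without waiting for contact with the Sponsor or the primary investigator. Both are notified as soon as possible and at the latest within 24 h.

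State the same rule in {17b}. The 24 h limit is borrowed from serious adverse event reporting, so sites would work to a deadline they already have.

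The cost is two sentences, the matching site instruction and IRB approval of the amendment, with no extra patients, visits or staff. The drawback is that the Sponsor can no longer question an opening beforehand. Two restraints remain: the recorded reason for each unblinding and the 20% limit on letter openings.

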### Definition of analysis population relating to protocol nonadherence {20c}

The intent-to-treat (ITT) population is defined as all randomized patients, whether or not the patient received the assigned treatment. The ITT patients will be analyzed according to the treatment assigned at randomization. The ITT population includes the patients who agree to enroll in the study and sign an informed consent form. However, ITT population involves those who have never received study drugs or never completed observation records. Efficacy analyses will be conducted for the modified intent-to-treat (mITT) population. This is defined as all patients randomized who received at least one dose of *QZQG* formula and were centrally assessed as RT-PCR positive for influenza at any timepoint, with patients grouped according to the treatment assigned at randomization. The per-protocol set is used to analyze the main outcome for evaluating efficacy and to examine the consistency of the results from the mITT. The PPS is defined as follows: (1) full compliance with inclusion and exclusion criteria; (2) the compliance of medication consumption is over 80%; (3) the patients complete the test and record of the outcome and safety evaluation at every time node; and (4) completion of the clinical trial without major protocol violation. The safety analysis set (SAS) is defined as patients who received any amount of study treatment. Patients will be analyzed according to the treatment received. Patients who were randomized to the study but who did not receive any study drug will not be included in the safety population. The SAS will be used for the analysis of all safety indicators. Multiple imputation will be used for missing data.

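### The order to exclude emergency-unblinded patients does not say from what; read as exclusion from the analysis, it is outcome-related and conflicts with the plan's own analysis sets

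*Protocol article*

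**What the plan says.** Section {16a}–{16c} of the protocol article sets the trigger: "In any emergency medical situation, such as serious adverse event or deteriorative condition, the unblinding process will be started", once the sponsor and the primary investigator have been contacted. Investigators at the lead centre must then "record the details of urgent unblinding and make sure the corresponding patient is excluded". The next sentence sets a limit: "If the rate of drug blinding leakage or emergency letter opening rises more than 20%, this trial will be considered as failure".

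Section {17b}, which is devoted to unblinding, asks for the date, time and reason to be recorded. It mentions no exclusion.

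Section {20c} defines the analysis sets:
- ITT: "The intent-to-treat (ITT) population is defined as all randomized patients, whether or not the patient received the assigned treatment". It adds: "The ITT patients will be analyzed according to the treatment assigned at randomization".
- Efficacy set: "Efficacy analyses will be conducted for the modified intent-to-treat (mITT) population". Membership depends on dosing and central RT-PCR positivity, with patients grouped as randomized.
- Safety set: everyone who received any study treatment.
- Per-protocol set (PPS): requires, among other things, completion without a major protocol violation.

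None of these definitions names emergency unblinding as a reason for removal.

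On the unblinding material itself, section {16a}–{16c} says: "An emergency letter including the random sequence and assignment has been prepared in all of centers". Section {17b} says that "the investigator will be supplied with a set of emergency envelopes".

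**The concern.** The named triggers are bad clinical outcomes, and such patients are more likely than others to miss the primary endpoint of clinical improvement within 7 days. Dropping them would raise the observed improvement rate in the arm they leave. If one arm has more such events, that arm gains. The comparison would then no longer be between the groups formed by randomization, and the error could go in either direction.

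The article also gives two answers to the question of who is analysed. One section orders an exclusion that the definitions of the efficacy, ITT and safety sets do not allow for. A team applying both texts at the blind data review would have to choose between them.

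**Working it through.** **Comparison of the passages.**

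| Section | What happens to an emergency-unblinded patient |
|---|---|
| {16a}–{16c} | Excluded; from what is not stated |
| {17b} | Unblinding is documented; nothing more |
| {20c} ITT | Stays, as randomized |
| {20c} mITT | Stays if the dosing and RT-PCR conditions are met |
| {20c} safety set | Stays if any study treatment was received |
| {22}, critically ill participants | Study drug is stopped; follow-up continues |

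Only the first row removes anyone.

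**Size if the exclusion reaches the analysis.** The plan gives no figure for this effect, so there is none to reproduce. Inputs from the documents are a placebo improvement rate of 50% and a total of 228 patients, hence 114 per arm at 1:1 (section {14}), and a two-sided 5% test (section {20a}). The exclusion rates are assumptions.

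Let p be an arm's true improvement rate and u the fraction excluded. If all excluded patients are non-improvers, the observed rate is p/(1 − u). With p = 0.50 in both arms:

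| Excluded, placebo / QZQG | Placebo | QZQG | Spurious difference |
|---|---|---|---|
| 5% / 5% | 0.50/0.95 = 52.6% | 52.6% | 0 |
| 1% / 2% | 0.50/0.99 = 50.5% | 0.50/0.98 = 51.0% | +0.5 points |
| 2% / 10% | 0.50/0.98 = 51.0% | 0.50/0.90 = 55.6% | +4.5 points |
| 5% / 15% | 0.50/0.95 = 52.6% | 0.50/0.85 = 58.8% | +6.2 points |

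**Opposite direction.** Take true rates of 70% for QZQG and 50% for placebo, and exclude 10% of QZQG and 20% of placebo patients. Then 0.70/0.90 − 0.50/0.80 = 77.8% − 62.5% = +15.3 points, against a true +20.

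**Effect on the test, 5% / 15% case, no true effect.** The numbers remaining are 114 × 0.85 = 96.9 for QZQG and 114 × 0.95 = 108.3 for placebo. The pooled rate is 114/205.2 = 0.556. The standard error is 0.0695 under the null and 0.0693 unpooled. The chance of a significant result favouring QZQG is Φ[(0.0619 − 1.96 × 0.0695)/0.0693] = Φ(−1.07), about 14%. With nobody excluded it is 2.5%.

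**If not all excluded patients are non-improvers.** With a fraction q of non-improvers among them, the observed rate is [p − u(1 − q)]/(1 − u). For the 5% / 15% case with q = 0.75, QZQG is (0.50 − 0.0375)/0.85 = 54.4% and placebo is (0.50 − 0.0125)/0.95 = 51.3%. The difference is +3.1 points, half of the +6.2. At q = 0.50, the same as in the whole arm, the bias is zero.

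**The case against.** The strongest reply is that *excluded* has no object and stands in a section on allocation and concealment. It may mean only that the patient leaves study treatment. If outcomes are still collected and analysed, there is no analysis bias. Section {20c} is where analysis sets are defined, and it keeps these patients. Section {22} continues follow-up of critically ill participants. This stands: removal from the analysis is a possible reading and not an established fact. It does not make the sentence harmless, because stopping study drug is already covered in sections {11b} and {22}. If the word meant an end to data collection, the lost outcomes would fall under the multiple imputation named in {20c}. Unless the imputation used the deterioration, it could credit such patients with improvement.

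Four stronger inferences are tempting, and the documents do not support them:

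- **That harm would be hidden.** Section {22} has every adverse event recorded regardless of relationship and serious ones reported within 24 h, and the safety set keeps everyone treated. Harm would be lost only if the one word overrode all of this.
- **That the plan accepts 45 exclusions** (0.20 × 228 = 45.6). The 20% limit counts blinding leakage as well as letter openings, and only urgent unblinding carries the exclusion. It is a ceiling for calling the trial failed, not an expected number.
- **That a bias of several points is to be expected.** No unblinding rates are given. Section {17b} restricts unblinding to what the patient's safety requires, so rates may be low or balanced. Follow-up runs to day 28, so a patient unblinded after day 7 may already count as improved; excluding that patient would lower the arm's rate.
- **That one opened letter reveals a whole centre's allocations.** The letter's wording permits this, but {17b} describes a set of envelopes and the opening of a single one for a single patient. The two descriptions differ; wider unblinding is not shown.

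**Conclusion.** The concern holds as a conflict within the document on who is analysed. Section {16a}–{16c} orders an exclusion without an object. Read as exclusion from the trial or the analysis, it depends on outcome, follows randomization, and contradicts the ITT, mITT and safety set definitions in {20c} and the recording-only rule in {17b}. The mITT conflict matters most, because efficacy is analysed in that set.

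On that reading the spurious difference runs from 0 (equal rates) through about +0.5 points (1% against 2%) to +6.2 points (5% against 15%), in favour of the arm with more events. These figures assume a 50% improvement rate in both arms, every excluded patient a non-improver, and exclusion rates that the documents do not supply. They show what the sentence could do and do not forecast what it will do. If the word means only leaving study treatment, with outcomes retained, the bias is zero and only the wording needs repair.

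The emergency letter and envelope descriptions are a separate, minor inconsistency on which this conclusion does not depend.

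**What to change.** In section {16a}–{16c}, replace the exclusion clause with a statement to this effect: emergency-unblinded patients remain in outcome follow-up and in the ITT, mITT (if they meet its criteria) and safety sets as section {20c} defines them; the unblinding is recorded as a protocol deviation; any exclusion for this reason is confined to the PPS or to a sensitivity analysis.

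Also reconcile the letter in {16a}–{16c} with the envelopes in {17b}, and state that each opening reveals one patient's allocation only.

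The cost is a short wording change and a check of the envelope sets at the centres. No new variable or visit is needed, and the criteria for unblinding or stopping study drug are untouched. The change should be made before database lock, so that no choice between the two texts is left to the data review.
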